### Outcome measures

#### Primary outcome: hot flash score

The primary outcome will be the mean change in the hot flash score from baseline to 8 weeks. The hot flash score for each day will be calculated as the number of hot flashes multiplied by the average severity of the hot flashes on that day. Participants will record the number of hot flashes in a daily diary during the trial. Flashes will be scored by severity on a scale from 0 to 4 (normal 0, mild 1, moderate 2, severe 3, and very severe 4) [33]. Since the hot flash score does not have a highest value, the residual hot flash score will be used for all statistical analyses. The hot flash score measured at the baseline will be normalized to 100, and the residual hot flash score will be calculated as a percentage of the baseline score.

#### Secondary outcomes

The secondary outcomes will be the mean changes in MRS, follicle-stimulating hormone levels, and estradiol levels, from baseline to 8 weeks. The MRS questionnaire is a self-administered instrument that has been widely used and validated. It has been used to assess the severity of menopausal symptoms in numerous clinical trials and epidemiological studies, and in research on the etiology of menopausal symptoms. The MRS questionnaire considers 11 symptoms, with each symptom being scored on a scale from 0 (no complaints) to 4 (very severe symptoms). The follicle-stimulating hormone and estradiol levels will be evaluated by blood tests on visits 1 and 18.

### Sample size

All analyses will be undertaken by a professional statistician. Because no prior research using hominis placenta pharmacopuncture to treat hot flashes has been published, we will reference studies that have used acupuncture alone [34] or human placenta extract alone [35, 36] to alleviate hot flashes. The standard deviation was conservatively assumed based on this previous research [34–36]. The population mean of the control group was estimated using the change from the baseline in studies of acupuncture, and the population mean of the treatment group was estimated by assuming that pharmacopuncture will be more effective than acupuncture alone. Hence, the effect value was calculated by combining estimates from studies of pure acupuncture with the weighted average from studies of herbal medications.

A minimum of 68 women in the treatment group and 34 women in the control group will be necessary to identify a 20% difference with a power of 80% and α = 0.05. Assuming a total withdrawal and dropout rate of 20%, we estimate that a total sample size of 128 subjects (85 in the treatment group and 43 in the control group) is required.

### Study visit and data collection

The schedule of follow-up visits is shown in Table 2.

**Table 2 Tab2:** Schedule of follow-up visits

Period	Screening	Treatment																	Follow-up
Visit	1	2	3	4	5	6	7	8	9	10	11	12	13	14	15	16	17	18	19
Week	0	1		2		3		4		5		6		7		8		9	13
Enrollment:																			
Informed consent	×																		
Demographic characteristics	×																		
Medical history	×																		
Vital signs	×	×	×	×	×	×	×	×	×	×	×	×	×	×	×	×	×	×	×
Physical examination	×																	×	
Lab test	×																	×	
Inclusion/exclusion criteria	×																		
Randomization		×																	
Intervention:																			
Pharmacopuncture group		×	×	×	×	×	×	×	×	×	×	×	×	×	×	×	×	×	
Control group		×	×	×	×	×	×	×	×	×	×	×	×	×	×	×	×	×	
Assessment:				×		×		×		×		×							
Hot Flash Score	×	×		×		×		×		×		×		×		×		×	×
Menopause Rating Scale		×								×								×	×
Adverse events		×	×	×	×	×	×	×	×	×	×	×	×	×	×	×	×	×	×

### Statistical analysis

The analysis will primarily be a full analysis. In addition, a per-protocol analysis will be undertaken. The full analysis will include all participants who have completed at least one PLC or NS treatment session and whose primary outcome has been evaluated at least once. The per-protocol analysis will include only those patients who have completed at least 80% of the treatment sessions and for whom there are no serious violations of the protocol. For the safety assessment, we will analyze a safety group, which will include all participants who have received at least one session of PLC or NS treatment. Important variables that may affect the final evaluation will be considered in the analysis.

### Missing data

If data are missing for some time point or the participant has been lost to follow-up, a last observation carried forward analysis will be performed, as if it were obtained at that time. The last observation carried forward method will be applied to all efficacy assessment analyses. However, for laboratory test results, the analysis will be performed using only the available data sets.

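### Last observation carried forward is the only missing-data method fixed for the hot flash score and the MRS, and it can bias the week-8 treatment difference in either direction

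*Protocol article*

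**What the plan says.** The Missing data section of the protocol article covers both isolated gaps and loss to follow-up: "If data are missing for some time point or the participant has been lost to follow-up, a last observation carried forward analysis will be performed", with the carried value treated as if measured at the missing time. It then generalises: "The last observation carried forward method will be applied to all efficacy assessment analyses". One exception follows: "for laboratory test results, the analysis will be performed using only the available data sets". No other method for efficacy data is named.

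The outcomes concerned are these:

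- **Primary.** "The primary outcome will be the mean change in the hot flash score from baseline to 8 weeks", analysed as a residual score with baseline set to 100.
- **Secondary.** "The secondary outcomes will be the mean changes in MRS, follicle-stimulating hormone levels, and estradiol levels, from baseline to 8 weeks". The two hormone levels are laboratory results and fall under the exception, which leaves the MRS under the carry-forward rule.

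The Design and setting section and Table 2 have the diary returned at visits 4, 6, 8 and so on to 18, about once a week. The MRS is taken at visits 2, 10, 18 and 19. Visit 19 comes 4 weeks after visit 18.

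The Sample size section plans for attrition ("Assuming a total withdrawal and dropout rate of 20" per cent) without a split by arm. It takes the control mean from the change seen in acupuncture studies. The Discussion expects saline injection to do better than acupuncture alone. The full analysis set requires at least one treatment session and a woman "whose primary outcome has been evaluated at least once".

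**The concern.** Carrying forward assumes that a woman's score stops changing on the day she leaves. The plan expects scores to fall in both arms, so on average a dropout is given a week-8 score that is too high. The error in each arm's mean is the dropout proportion times the improvement that dropouts had still to make. The treatment difference is biased by the gap between the two arms' errors, and nothing in the plan makes them equal.

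The MRS is more exposed because it is measured rarely. A woman who leaves before visit 10 has only her visit 2 value to carry, so she counts as unchanged. At visit 19 a value taken during treatment would stand in for one taken 4 weeks after treatment ended.

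At stake are the size of the primary effect, the power to detect it, and, if saline loses more women, the false-positive rate. The weekly diary data that would avoid most of this are already being collected.

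**Working it through.** **The plan's own figure.** 68/0.8 = 85 and 34/0.8 = 42.5, rounded up to 43, total 128. This reproduces the stated sample size.

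**Implied SD.** The document gives none. Solving the two-sample formula for 68 and 34 women, a 20-point difference, 80% power and 5% two-sided (sidedness is an assumption):

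SD = 20 × √(34 × 68/102) / (1.960 + 0.842) = 34.0.

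With 85 and 43 women the standard error is 34 × √(1/85 + 1/43) = 6.36.

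**Bias formula.** Assume a linear course from 100 to an end value *E* at week 8, completely random dropout, and the last observation spread evenly over weeks 1 to 7. The mean carried value is then midway between 100 and *E*, so

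expected arm mean = *E* + *d* × (100 − *E*)/2,

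where *d* is the arm's dropout proportion. The end values and the splits by arm below are assumptions. Unless noted, each split gives 20% overall, for example (0.15 × 85 + 0.30 × 43)/128 = 20.0%.

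**No true effect**

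| Both arms end at | Dropout PLC / NS | Spurious PLC benefit | Type I error |
|---|---|---|---|
| 50 | 15% / 30% | 0.30×25 − 0.15×25 = 3.75 | 9.1% |
| 60 | 15% / 30% | 0.30×20 − 0.15×20 = 3.0 | 7.7% (simulated) |
| 60 | 25% / 10% | 0.10×20 − 0.25×20 = −3.0 | 7.2% (simulated) |
| 60 | 20% / 20% | 0 | 5.1% (simulated) |

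The 9.1% is P(|Z + 3.75/6.36| > 1.96). The simulated rates use 20,000 runs of a t test with SD 33.6 and within-woman correlation 0.7. If the response comes earlier, the 3.0 points at 15%/30% fall to 1.65 (exponential approach) or 1.3 (plateau from week 4).

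**True difference of 20 points (NS ends at 70, PLC at 50)**

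| Dropout PLC / NS | NS mean | PLC mean | Difference | Simulated power |
|---|---|---|---|---|
| 20% / 20% | 70 + 0.20×15 = 73.0 | 50 + 0.20×25 = 55.0 | 18.0 | 78% |
| 25% / 10% | 70 + 0.10×15 = 71.5 | 50 + 0.25×25 = 56.25 | 15.25 | 63% |
| 15% / 30% | 70 + 0.30×15 = 74.5 | 50 + 0.15×25 = 53.75 | 20.75 | 88% |

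**When the bias vanishes.** On this linear course it is zero when *d*(100 − *E*) is the same in both arms. With ends 70 and 50, dropout of 15% on PLC and 25% on NS gives 73.75 − 53.75 = 20.0, no bias despite unequal dropout (18% overall). If neither arm changes, 15%/30% also gives zero bias.

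**Does the replacement help?** In 4,000 simulated trials of the first null case (correlation 0.7, random dropout), a likelihood estimate of the week-8 difference from the same weekly data was within 0.1 point of zero (Monte Carlo standard error 0.11), where carrying forward is off by 3.75.

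**The case against.** The strongest reply has four parts.

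**Unequal dropout is only supposed.** The document gives 20% in total, and participants are blinded. It is true that no imbalance is documented, and a very lopsided split such as 10% against 40% would have no basis. But the treating doctors can tell the products apart, so a moderate imbalance is plausible. Equal dropout still costs 2 points of a true 20 when the arms improve by different amounts.

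**The sizes are modest.** Under no true effect the bias is 1.3 to 3.75 points against a 20-point target. That is fair. It makes this a correctable weakness, not a fatal one.

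**The per-protocol analysis is a check.** It requires 80% of sessions, so early leavers drop out of it. It is a partial check only, because it is a selected population and not the primary analysis.

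**This could be left to the analysis plan.** The absence of further sensitivity analyses could be. The carry-forward rule is not left open: the protocol states it, and an analysis plan that follows the protocol inherits it.

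A reader might also infer several stronger points that the document does not support:

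- *Every efficacy outcome is affected.* FSH and estradiol, two of the three secondary outcomes, are exempt.
- *Unequal dropout always biases the result.* The working shows that it is neither necessary nor sufficient.
- *Standard errors are materially wrong.* The simulation with equal dropout and no effect keeps type I error at 5.1%, so no such distortion appears there.
- *A persistence claim at visit 19 is compromised.* No such claim is made; visit 19 is a follow-up assessment.
- *Women without a post-baseline score are dropped.* The full-analysis wording does not say post-baseline, and Table 2 schedules the score at visits 1 and 2. Such women may be excluded, or may enter with baseline carried forward.

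**Conclusion.** The concern holds for the hot flash score and the MRS. The protocol fixes one method that, on the plan's own expectation of improvement in both arms and 20% dropout, gives a biased week-8 difference unless the two arms' errors happen to cancel. The direction cannot be known in advance, so the method cannot be defended as conservative.

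On the assumed courses and splits, the false benefit under no effect is 1.3 to 3.75 points when saline loses more women, with type I error up to about 9%. A true 20 points is reported as 15.25 when PLC loses more, and power falls to 63%.

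These figures rest on an SD back-solved from the sample size, assumed end values, completely random dropout and assumed splits by arm. They show the mechanism and plausible size and do not forecast this trial's result. The MRS points follow from the visit schedule alone.

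**What to change.** Amend the Missing data section of the protocol, and the analysis plan to match, before any comparative data are seen.

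- **Primary analysis.** Fit a likelihood-based mixed model for repeated measures to the residual hot flash scores returned at visits 4 to 18. Include treatment, visit, treatment-by-visit, baseline score and hospital, and report the treatment contrast at the primary time point. The baseline covariate must be the raw score, since the residual score is 100 for everyone at baseline.
- **MRS.** Use the same type of model for visits 10, 18 and 19.
- **Carrying forward.** Keep it at most as a sensitivity analysis, and do not carry treatment-period values into visit 19.

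The cost is a protocol amendment while recruitment is open, which the ministry and three review boards that approved the current text may need to see, plus some programming. The model relies on data being missing at random, which cannot be verified. No new data and no additional patients are needed; the total of 128 stands.

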### Additional analysis

#### Safety evaluation

At each visit, all subjective and objective discomforts will be collected through interviews, and these will be recorded on the case report form. The overall rate of adverse events will be calculated and analyzed. The rate of adverse events for each group will be compared using a chi-squared test or Fisher’s exact test. If it is necessary to control critical variables that may affect the final assessment, a layering analysis will be applied (e.g., the Cochran–Mantel–Haenszel method).

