### Design and setting

This will be a randomized placebo-controlled single-blind multi-center parallel-design clinical trial. Participants will be enrolled from three hospitals: Ilsan Korean Medicine Hospital of Dongguk University, Gwangju Korean Medicine Hospital of Wonkwang University, and Dunsan Korean Medicine Hospital of Daejeon University. The study process is illustrated in Fig. 1. In accordance with the protocol, all subjects who sign the informed consent will undergo a 2-week screening period before commencing treatment. Subjects who complete the screening period and meet the selection criteria will be randomly assigned to one of two groups for 8 weeks: the treatment group, who will receive the PLC pharmacopuncture treatment, and the placebo group, who will receive injections of normal saline (NS). The relevant treatment material will be administered twice a week for 8 weeks (a total of 16 injections). From the second visit onwards, all subjects will receive a hot flash symptom diary, which they will be asked to bring to visits 4, 6, 8, 10, 12, 14, 16, and 18. The Menopause Rating Scale (MRS) will be assessed at visits 2, 10, and 18 for both groups. The post-treatment follow-up assessment will occur at visit 19, when the symptom diary and MRS questionnaires maintained by the subjects will be assessed for both groups (Figs. 1 and 2).

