### Randomization

Eligible participants will be randomized into one of the two groups via stratified block randomization at the hospital where they first come into contact with the research coordinators. The stratification factor is the hospital. A separate randomization sequence will be generated by computer at the central coordinating center by an independent statistician. The randomization codes will be sealed in opaque envelopes. Randomization plans will be kept confidential, except for emergencies. In the event of adverse events and emergencies related to the safety of the subjects, the test conductor in charge can identify the assigned treatment group of the subject through the statistician, who will maintain the random assignment table.

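### The default adverse-event comparison ignores hospital, the stratification factor, and so would lose some power to detect harm if event rates differ between hospitals

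*Protocol article*

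**What the plan says.** The Safety evaluation section of the protocol article names the between-arm test: "The rate of adverse events for each group will be compared using a chi-squared test or Fisher’s exact test". Both tests pool the hospitals. The same section then adds a conditional step, with CMH as its example: "If it is necessary to control critical variables that may affect the final assessment, a layering analysis will be applied". It names neither the variables nor what would make the step necessary.

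On design, the Design and setting section states "Participants will be enrolled from three hospitals", and the Randomization section states "The stratification factor is the hospital". No other stratification factor is given. The Sample size section plans 85 women on treatment and 43 on control. No power, error rate or expected event rate is attached to the adverse-event comparison. The safety group is everyone who received at least one session, so up to 128 women.

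**The concern.** Randomization within hospital balances the arms across hospitals, so the pooled difference in event rates is not biased by hospital. The pooled standard error, however, still includes variation between hospitals that the design has already removed from the comparison. If hospitals differ in their event rates, the test rejects less often than its nominal 5% under no effect and has less power when there is a real excess.

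Differences between hospitals are plausible, because discomforts are elicited by interview at every visit in three separate institutions. They are not documented. Safety is one of the trial's two stated aims and the control arm is small, so power given up without need is worth recovering. The protocol already names a method that recovers it, but does not tie that method to hospital and makes its use optional.

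**Working it through.** **The plan's own figure.** The only relevant figure is the sample size. With 20% dropout, 68/0.8 = 85 and 34/0.8 = 42.5, rounded up to 43, total 128. This reproduces. There is no stated figure for the adverse-event comparison to reproduce.

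**Inputs from the article.** 85 against 43 women, three hospitals, randomization stratified by hospital.

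**Assumed inputs.** Event rates by hospital, hospital sizes (about equal, or 75/30/23), about 2:1 allocation within each hospital, two-sided 5% level.

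**Step 1: width of the pooled standard error.** With arms balanced within hospitals of equal size, the pooled test uses the variance p̄(1 − p̄), where p̄ is the mean rate. The variance that applies is the mean of p_h(1 − p_h) over hospitals. The inflation factor is f = √[p̄(1 − p̄) / mean p_h(1 − p_h)], and the approximate null rejection rate is 2[1 − Φ(1.96 f)].

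- 15/20/25%: f = √(0.16/0.1583) = 1.005; null rate about 4.9%.
- 10/20/30%: f = √(0.16/0.1533) = 1.02; about 4.5%.
- 5/20/35%: f = √(0.16/0.145) = 1.05; about 4.0%.
- 10/30/50%: f = √(0.21/0.1833) = 1.07; about 3.6%.
- 5/20/50%: f = √(0.1875/0.1525) = 1.11; about 3.0%.
- Equal rates: f = 1; nothing is lost.

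**Step 2: simulation.** The pooled statistic is (p_T − p_C)² / [p(1 − p)(1/85 + 1/43)]. The CMH statistic, without continuity correction, is [Σ(a_h − E_h)]² / ΣV_h. Here a_h is the number of treated women with an event in hospital h, and E_h and V_h are its hypergeometric mean and variance. There were 40,000 or 100,000 simulated trials per setting. Results are chi-squared against CMH.

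| Control rates by hospital | Effect | Null rejection | Power |
|---|---|---|---|
| 20% in each | rate ratio 1.6 | 5.0% vs 5.0% | 29% vs 29% |
| 15/20/25% | rate ratio 1.6 | 4.9% vs 5.0% | 28.4% vs 29.4% |
| 10/20/30% | rate ratio 1.6 | 4.6% vs 5.0% | 28% vs 31% |
| 10/20/30% | odds ratio 3 | 4.4–4.5% vs 4.8% | 62–69% vs 66–72% |
| 5/20/35% | rate ratio 1.6 | 4.1% vs 5.0% | 27% vs 34% |
| 10/30/50% | rate ratio 1.6 | 3.5% vs 4.9% | 49% vs 61% |
| 5/20/50% | odds ratio 3 | 2.9–3.4% vs 4.9–5.0% | 41–52% vs 56–67% |

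Ranges cover equal and unequal hospital sizes. The figures move with the hospital split and the effect measure, so they show order of magnitude only. The null rates agree with step 1.

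**Step 3: does free choice of test inflate error?** Rejecting whenever any of chi-squared, Fisher or hospital-CMH rejects gave a type I error of at most 5.2% across all settings run.

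**Step 4: exact tests.** Fisher's test is conservative in itself: 3.7–3.8% under no effect at 20% in every hospital. An exact stratified test is conservative too. At 5% in every hospital it rejects 2.6% under no effect, against 3.8% for both chi-squared and CMH. At 20% in every hospital its power at rate ratio 1.6 is 25.6%, against 28.8% for chi-squared.

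**The case against.** The strongest reply is that unstratified tests are conventional for adverse-event tables, that this comparison is unpowered, and that nothing in the article shows hospitals to differ. The article sets one interview procedure, common quality standards and central monitoring. At moderate spread the gain is only 1 to 4 points, on a test whose power at rate ratio 1.6 is about 30% either way. The article also already mentions CMH, and the trigger and variables may be set out in an analysis plan that is not shown. Most of this stands and keeps the point small. It does not remove it: the article states a default test, that default leaves out the stratification factor, and a better default is available at no cost in data. The unspecified trigger and variables are not themselves counted against the article.

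Three stronger readings are tempting and are not supported:

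- A reader might infer that the planned comparison is conservative in any event. For chi-squared against CMH this needs rates that differ between hospitals, and the documents give none; with equal rates the two tests agree. Fisher's own conservatism has nothing to do with stratification.
- A reader might infer that the open condition lets the analyst pick a test and so inflates false positives. Step 3 shows no material inflation for the three tests named, and the choice between chi-squared and Fisher normally follows expected cell counts. Selection among other, unnamed variables was not examined.
- A reader might infer that stratifying never has a downside. That fails for the exact stratified version (step 4).

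**Conclusion.** The point holds in a limited and conditional form. The default safety test leaves out the only stratification factor, and it loses power to detect harm to the extent that event rates differ between hospitals. Under assumed rates the loss is about 1 to 4 points at moderate spread, about 7 to 15 points at wide spread, and nil at equal rates. These figures rest on 85 against 43 women, roughly 2:1 allocation within each hospital, and rate ratios of 1.6 or odds ratios of 3, none of which the article states for adverse events except the arm sizes. The error is towards missing a harm, not towards a false alarm. It is a free improvement to a secondary analysis; the primary outcome and the sample size are untouched.

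**What to change.** In the Safety evaluation section, or in the analysis plan that implements it:

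- Make the CMH test stratified by hospital, reported with the stratified risk difference, the planned comparison of women with at least one adverse event.
- Remove the necessity condition as far as hospital is concerned. It may stay for other variables.
- Keep the unstratified chi-squared or Fisher test as a descriptive check.
- If an exact test is used for sparse events, state that it is itself conservative, as Fisher's test is.

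The cost is one sentence or two. No extra data are needed, and the asymptotic CMH test gave up no meaningful power where hospitals had equal rates (at odds ratio 3 and 20% in each hospital, 75% against 75–76%).
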